## Abstract

**Background:**

Minimally invasive incisional hernia repair has been established as a safe and efficient surgical option in most centres worldwide. Laparoscopic technique includes the placement of an intraperitoneal onlay mesh with fixation achieved using spiral tacks or sutures. An additional step is the closure of the fascial defect depending upon its size. Key outcomes in the evaluation of ventral abdominal hernia surgery include postoperative pain, the presence of infection, seroma formation and hernia recurrence. TACKoMESH is a randomised controlled trial that will provide important information on the laparoscopic repair of an incisional hernia; 1) with fascial closure, 2) with an IPOM mesh and 3) comparing the use of an articulating mesh-fixation device that deploys absorbable tacks with a straight-arm mesh-fixation device that deploys non-absorbable tacks.

**Methods:**

A prospective, single-centre, double-blinded randomised trial, TACKoMESH, will establish whether the use of absorbable compared to non-absorbable tacks in adult patients undergoing elective incisional hernia repair produces a lower rate of pain both immediately and long-term. Eligible and consenting patients will be randomized to surgery with one of two tack-fixation devices and followed up for a minimum one year. Secondary outcomes to be explored include wound infection, seroma formation, hernia recurrence, length of postoperative hospital stay, reoperation rate, operation time, health related quality of life and time to return to normal daily activity.

**Discussion:**

With ongoing debate around the best management of incisional hernia, continued trials that will add substance are both necessary and important. Laparoscopic techniques have become established in reducing hospital stay and rates of infection and report improvement in some patient centered outcomes whilst achieving similarly low rates of recurrence as open surgical techniques. The laparoscopic method with tack fixation has developed a reputation for its tendency to cause post-operative pain. Novel additions to technique, such as intraoperative-sutured closure of a fascial defect, and developments in surgical technology, such as the evolution of composite mesh design and mesh-fixation devices, have brought about new considerations for patient and surgeon. This study will evaluate the efficacy of several new technical considerations in the setting of elective laparoscopic incisional hernia repair.

**Trial registration:**

Name of registry - ClinicalTrials.gov Registration number: NCT03434301. Retrospectively registered on 15th February 2018.

## Background

An incisional hernia is an abdominal hernia that occurs at the site of a previous surgical incision through which access to the abdominal cavity has been obtained and is the result of a failure of abdominal wall closure. The incidence of incisional hernia following laparotomy is historically quoted as up to 20%. It is estimated that in Europe over 80,000 incisional hernias become symptomatic annually but there is a lack of consensus regarding their optimal management [1]. Incisional hernias enlarge over time and can result in serious complications such as pain, bowel obstruction, strangulation and enterocutaneous fistula. Furthermore, the quality of life and chances of employment are reduced in patients suffering with an incisional hernia [2].

Recurrence rates in the management of incisional hernia remain unacceptably high; reports as high as 33% after first repair and 44% after second repair [3]. This has significant implications in terms of morbidity and socioeconomic cost. Recurrence rates are comparable for open and laparoscopic methods of repair [1].

It is now accepted that only relatively small (less than 3 cm) incisional hernias should be repaired via primary tissue approximation with sutures alone [4]. Open mesh techniques commonly used for larger hernias include the sublay (Rives-Stoppa) operation and the onlay (Chevrel) operation. The sublay technique has been reported to be more complicated and time consuming than the onlay repair but reports suggest a lower incidence of wound infection and seroma formation [2]. Wound complications after onlay repair may more rapidly lead to mesh infection because of the close and unprotected contact of the mesh with the subcutis. Uncontrolled studies have however also shown a low incidence of wound complications with the onlay method [4].

Laparoscopic repair is not always possible for large hernias. The size of the defect or the proximity of the defect to the costal margin or pelvis may render laparoscopic mesh placement difficult or unsuitable [1, 5]. Undertaking fascial closure prior to mesh placement is becoming more common place, with an emerging consensus that a hernia of up to 10 cm in diameter can be repaired using the laparoscopic technique [6]. These techniques include the use of intraperitoneal onlay mesh (IPOM) using a specially designed composite material secured with either spiral tacks or sutures. This type of mesh has been designed specifically to ensure good tissue integration whilst minimizing the risk of visceral attachments.

Goodney et al., identified 83 studies comparing open and laparoscopic incisional hernia repair from a structured Medline search [7]. This resulted in an overall comparison of 390 patients having open repair with 322 patients having laparoscopic repair. Perioperative complications and length of stay were reduced in the laparoscopic group. Frantzidees et al. identified 53 studies with a total of 5227 laparoscopic incisional hernia repairs; the rate of hernia recurrence was 3.98% [5]. This result was mostly the product of specialty centers in which minimally invasive surgery is prominent; the authors concluded that the true recurrence rate is likely to be higher. One of the first prospective randomised trials comparing open and laparoscopic repair of incisional hernia concluded that laparoscopic repair is associated with fewer, albeit more severe, complications and may improve some patient-centered outcomes [8].

Post-operative pain assessment has been examined as mesh-fixation with tacks is regarded as particularly painful. Reynvoet et al. demonstrated, upon examination of thirteen studies using either tack or suture fixation, that there was no real difference in pain score or recurrence [9]. However, no strong conclusions can be drawn from what is very heterogeneous data. With any mesh-fixation technique, transfascial sutures or the use of tacks, there remains a risk of chronic pain due to nerve damage as well as mesh migration. Although the tensile strength of sutures has been shown to be greater, in a laparoscopic pig model, no fixation technique was shown to be superior [10]. A randomised trial published in 2009 compared three fixation techniques; absorbable sutures with tacks, double crown technique with tacks only and non-absorbable sutures with tacks [11] (Table 1). The question here was whether sutures were better in combination with tacks or tacks alone, note that the fascial defect was not closed in any arm. No technique was found to be superior with the primary end-point being pain. Muysoms, in 2013, compared in a trial setting, spiral tacks using a double crown technique with transfasical sutures with a single crown technique, no fascial closure was attempted in this study with a leaning towards reduced recurrence with the double crown technique [12].

**Table 1 Tab1:** A summary table depicting the randomised controlled trials undertaken to date comparing differing mesh fixation techniques in laparoscopic incisional hernia repair using intraperitoneal (IPOM) mesh

Author	Year	Number	Comparison	Result	Conclusion
Wassenaar et al. [11]	2010	199	3 groups: 1) Absorbable sutures with tacks, 2) Double crown with tacks, 3) Nonabsorbable sutures with tacks No FASCIAL CLOSURE	No difference with any group	More tacks with DC group and it was quicker (*p* = 0.03)
Muysoms et al. [12]	2013	76	Double crown technique DC v sutures and single crown technique SC	DC group operating time was shorter (*p* = 0.014), DC also had a reduced pain score at 4 weeks and at coughing (*p* = 0.028/*p* = 0.013), also at 3 months (*p* = 0.036)	DC technique was quicker and provided less pain up to 3 months but there was no difference in recurrence
Bansal et al. [13]	2012	110	Tack v suture fixation	Higher cost with tacks (*P* < 0.001). Suture fixation more cost effective than tacks Qol No difference	Early post op pain preferredwith suture, but no other differences were noted

No difference in recurrence was shown in any study. No study included data following fascial closure. Studies comparing various mesh fixation techniques

The laparoscopic repair has been criticised for producing cosmetically worse results than the open repair. This is because the hernia sac is not excised and the defect not closed.

The method and choice of repair of incisional hernia remains one of ongoing debate. Key considerations in planning surgery include the size of the defect and its proximity to the costal margin and pelvis. Areas of interest in the debate include known post-operative complications, post-operative pain and rates of hernia recurrence. Additional considerations for the patient include that of cosmesis and post-surgery quality of life.

### Rationale

To date no randomised controlled trial has compared the use of absorbable or non-absorbable tack fixation for laparoscopic incisional hernia repair after fascial closure. This prospective randomised controlled trial proposes to assess pain scores as a primary measure to determine whether absorbable tacks may provide a benefit in reducing the risk of immediate and long-term pain. Additional evaluation will see whether the risk of serious adverse events (SAE) is affected. This information is needed to provide evidence of the optimal method for surgeons and policy makers.

## Methods

### Study design

A prospective, single-centre, observer and patient blinded (double blinded), fixed design randomised trial.

### Study setting and sponsorship

Manchester University Hospitals NHS Foundation Trust, within the National Health Service (NHS) in the United Kingdom (UK) is the trial sponsor and the trial will take place in the Manchester Royal Infirmary.

### Objectives

#### Primary objectives

To compare pain measured at rest and at activity with a visual analogue scale (VAS) at day 30 post-operation incurred from using absorbable tack fixation versus non-absorbable tack fixation with a composite mesh for the repair of midline abdominal incisional hernia in adult patients.

#### Secondary objectives

To examine changes in pain using VAS at days 1 and 6, 30 days and one year post-operation at rest and activity.To detect the presence of intermittent hyperaesthesia, burning sensation and or jabbing pain in the abdominal wall.To compare whether the method of fixation for an IPOM repair has an effect on the following outcomes (complications will be classified according to the Clavien Dindo):
Seroma formation at 30 days post operationLength of postoperative hospital stayOperating timeMesh fixation timeWound infection (SSI)Hernia recurrence at 1 yearTime to return to normal daily activity and workHealth related quality of life (QoL)Other adverse events

### Study population

#### Inclusion criteria

All adults undergoing elective incisional hernia repair for midline abdominal incisional hernia, with a defect of 3-10 cm in diameter.

Midline abdominal incisional hernia defined as any hernia that arises from a previous surgical incision in the anterior abdominal wall musculature providing that there is a minimum distance of 3 cm from the border of the defect to the costal margin or pelvis.

#### Exclusion criteria

Patients less than 18 years of age, or unable to give informed consentPatients over 80 years of ageClinically small incisional hernia < 3 cm maximum diameterRecurrent incisional herniaEmergency procedures (for irreducible, strangulated or obstructed hernia)Procedure involving purulent inflammation (e.g. abscess); preoperative perforation of gastrointestinal, biliary or genitourinary tract; penetrating trauma > 4 h old) or contaminated (Non-purulent inflammation; gross spillage from gastrointestinal tract; entry into biliary or genitourinary tract in the presence of infected bile or urine; major break in technique; penetrating trauma < 4 h old; chronic open wounds to be grafted or covered) surgeryFailure to close the anterior rectus sheath intraoperativelyPregnancyPrisonersPatients with a Body Mass Index (BMI) > 40 kg/m^2^Patients participating in any other study, whose concurrent participation in the TACK study might place them at undue risk or might confound the study data in the opinion of the chief investigators

### Study process

Following potential participant identification and recruitment from incisional hernia referrals in participating surgeons’ out-patient clinics the potential participant will be sent information about the study. A Patient Information Sheet (PIS) will be given to the participant as soon as the decision has been made to list the patient for incisional hernia repair. In all cases, patients will be given sufficient time to consider the implications of their participation (minimum of one week). Written informed consent to participate in the study will be obtained preoperatively, at the same setting where (normal) consent for the intended surgical procedure is obtained > 24 h prior to surgery, by the operating surgeon. Intraoperatively, the size of the hernia defect will be photographed next to a metric ruler as per the Surgeon’s Instructions. Standardised post-operative care will be used in keeping with the Surgeon’s Instructions. Pain assessments will be conducted at pre-operation then post operatively on days 1, 5–7, day 30 (primary end point) and 1 year.

### Trial randomisation

There will be two arms to the trial (*n* = 136):Mesh placement with absorbable tack fixation.Mesh placement with non-absorbable tack fixation.

Participants will be allocated in sequence to a unique identification number and randomised to one of two groups i.e. receive either absorbable or non-absorbable tack fixation, stratified by defect size (3-6 cm or > 6-10 cm). The participant randomisation procedure is shown below.

Patients who have given consent and are due to be operated on will be randomised by a sealed envelope randomisation.

The operating surgeon will select from the sealed envelopes the tack to be used for the TACKoMESH Trial on the morning of the patient’s planned surgery to obtain the randomisation allocation to treatment. The patient’s initials and date of birth will be entered into the randomisation allocation; a study number and the treatment allocation assigned to each patient. The study number and treatment allocation will automatically appear on the Study Randomisation Form. Following the appropriate procedure the completed online Study Randomisation Form will be printed by the operating surgeon, placed in a provided sealed envelope, and labelled as ‘TACKoMESH - Study Randomisation Form and Incisional Hernia Repair Operation Note’.

### Surgical technique

All cases will be performed with a Consultant surgeon scrubbed throughout the entire case. Prophylactic antibiotics will be given at the time of the induction of anaesthesia. Pneumoperitoneum will be established according each surgeon’s preferred method. Three ports will be used (2 × 11 mm and 1 × 5 mm).The fascial defect will be measured in cm when the adhesions have been dissected free with no pneumoperitoneum present.

Adhesiolysis will be carried out with intrabdominal pressure at 12-15 mmHg. Fascial closure will be achieved using a No 1 Loop Maxon at no more than 10 mmHg pressure (8–10 mmHg).

The Mesh used should be fixated with the choice of fixation device that the patient has been randomised to without the use of transfascial sutures ensuring that at least 3 cm cover has been achieved beyond the defect. The size of the mesh used will be also recorded and fixation will be applied at the edges of the fascial defect with the remaining tacks placed on the outer & inner rim (along the closure line) to secure the mesh and prevent folding; the double crown technique. The number of tacks used will be recorded.

In case of intra-operative contamination, the laparoscopic procedure may be abandoned and converted to open surgery.

The use of local anaesthetic (1% lidocaine or 0.25%/ 0.5% bupivicaine) infiltration is permitted and must be recorded on the CRF form. Skin closure using subcuticular 3.0 monocryl or skin staples ± skin glue cover is permitted and must be recorded on the CRF form. Wound dressings may be applied according to the surgeon’s usual practice at the end of the procedure and must remain unchanged for 24 h unless there is a clinical indication for changing the dressing.

### Blinding

In order to ensure continued blinding of the research team, once the surgical procedures have been completed, the Study Randomisation Form will be placed in a sealed and labeled envelope, and securely inserted into the patients’ hospital notes. This may be opened in emergency if necessary to assist in the patient’s continuing management, or if the patient returns to theatre should a re-operation be required. Theatre staff will be instructed not to divulge the patient’s randomisation allocation to anyone.

### Sample size

Primary outcome: Pain score at rest and activity at day 30 recorded using visual analogue pain score (VAS) (0–10).

Previous studies indicate that a good approximation for the standard deviation (SD) in VAS is 2. With an alpha of 0.05, 80% power and 20% dropout, a sample size of 74 (37 per group) is sufficient to detect a difference of 1.5 between the groups.

There has been a suggestion that a rate of attrition of 20% is un-necessarily high for this group of patients, and we also consider whether the difference is achievable, therefore we recalculate the sample size considering these changes:

With a power of 80%, an alpha of 0.05, SD 2 and dropout of 5%, a sample size of 136 (68 per group) is sufficient to detect a difference of 1 between the groups.

No interim analysis will be undertaken therefore no adjustment is required in the sample size. This is a fixed design and no sample size re-estimation will be performed during the course of the study.

### Outcomes

#### Primary outcome

Pain score at rest and activity at day 30 recorded using visual analogue pain score (VAS) (0-10 cm).

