### Statistical analysis

All analyses will be pre specified prior to data collection and conducted according to the intention-to-treat principle and presented in accord with CONSORT guidelines for the reporting of RCTs. All analyses will be conducted using R v3.0.2. All statistical tests will be 2-sided, and deemed to be statistically significant if *p* ≤ 0.05. The analyst will be blind to group allocation.

The primary outcome, VAS pain scores at day 30, will be explored via descriptive statistics and graphics. The scores in each of the groups will then be compared using an ANOVA with study group and defect size as factors. Secondary analyses will report all outcomes at each time-point using appropriate (parametric/non-parametric) descriptive statistics (frequencies [%] or mean/median [standard deviation (SD)/interquartile ranges (IQR)]) and graphics. The pre-operative variables will also be described via these methods.

VAS scores over time will be explored via a generalised linear model, using time, group and an interaction term as covariates. Operation time, mesh time, length of stay and time to return to normal daily activities will be compared between groups using descriptive statistics and independent t-test or Mann-Whitney U test as appropriate. Descriptive comparisons will also be made between the two defect size groups for each outcome. For secondary outcomes consideration for multiple testing will be included in the conclusions. Total numbers with any of seroma formation, wound infections or hernia recurrence at 30 days and 1 year will be reported with odds ratios.

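### The primary outcome names two day-30 pain scores, but the sample size covers one, so the stated 5% alpha and 80% power do not both hold if both scores are tested

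*Protocol article*

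**What the plan says.** The Primary objectives section reads "To compare pain measured at rest and at activity with a visual analogue scale (VAS) at day 30 post-operation". The Primary outcome section reads "Pain score at rest and activity at day 30 recorded using visual analogue pain score (VAS"), and the Sample size section opens with the same definition. Each names pain at rest and pain at activity together.

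The Sample size section then works with one SD, one difference and one alpha. Its conclusion is that "a sample size of 136 (68 per group) is sufficient to detect a difference of 1 between the groups". The inputs behind that figure are a single set: two-sided testing at 0.05, 80% power, an SD of 2 and 5% loss to follow-up. It says that the sample size needs no adjustment, and the only reason it gives is that there is no interim analysis.

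The Statistical analysis section says "The primary outcome, VAS pain scores at day 30, will be explored via descriptive statistics and graphics", followed by an ANOVA with study group and defect size as factors. On the threshold it says "All statistical tests will be 2-sided, and deemed to be statistically significant if" p is 0.05 or less. On multiplicity it says only "For secondary outcomes consideration for multiple testing will be included in the conclusions".

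**The concern.** Pain at rest and pain on activity are separate readings in the same patient, and an intervention can affect one without the other. The article calls both primary but does not say which of these applies:

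- one of them is the primary variable;
- they are combined into one number;
- either may carry the claim;
- both must be significant.

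The alpha and power belong to a single test of a single score. If two are tested, the operating characteristics depend on a rule that is not stated. A split result, with activity significant and rest not, could be reported as a positive or a negative trial under the text as it stands.

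**Working it through.** **Inputs from the Sample size section:** difference 1, SD 2, two-sided alpha 0.05, power 80%, dropout 5%, 68 per arm (136 in total).

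**Assumptions not in the article:** the same difference (1) and SD (2) apply to both scores. The within-arm correlation ρ between rest and activity is varied from 0 to 0.95. The defect-size factor in the ANOVA is ignored.

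**Step 1. Reproduce the plan's figure.** The standardised difference is 1/2 = 0.5. A two-sample t-test at 80% power needs 63.8, so 64 evaluable per arm, with power 80.1%. Allowing for dropout, 64/0.95 = 67.4, so 68 per arm and 136 in total. The superseded figure ("With an alpha of 0.05, 80% power and 20% dropout, a sample size of 74 (37 per group) is sufficient") also reproduces: 29/0.8 = 36.25, so 37 per arm. The arithmetic is sound for one score.

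**Step 2. Set up two scores.** With 64 per arm, each test statistic is approximately normal with mean 0 under the null. Under the alternative its mean is

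μ = 1 / (2 × √(2/64)) = 2.828.

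The two statistics have correlation ρ. The critical value is c = 1.960 at 0.05, and c_B = 2.241 at 0.025. In this normal approximation the power for one score is Φ(2.828 − 1.960) = 80.7%, against 80.1% from the t-test.

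**Step 3. Either score may carry the claim, each at 0.05.** Type I error = 1 − P(|Z1| ≤ c and |Z2| ≤ c). At ρ = 0 this is 1 − 0.95² = 9.75%. Power = 2 × 80.7% − P(both significant).

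**Step 4. Both must be significant, each at 0.05.** Power = P(Z1 > c and Z2 > c). Type I error is at most 5%.

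| ρ | Either: type I error | Either: power | Both: power |
|---|---|---|---|
| 0 | 9.75% | 96% | 65% |
| 0.5 | 9.1% | 92% | 70% |
| 0.7 | 8.35% | 89% | 72% |
| 0.8 | 7.8% | 88% | 74% |
| 0.9 | 7.0% | 86% | 76% |
| 0.95 | 6.5% | 84% | 77% |

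The last entry for either-score power is 2 × 80.7% − 77.3% = 84%.

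**Step 5. Alpha-controlled rules that keep both scores primary, at N = 136.**

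- Bonferroni at 0.025 each: power per score is 71% by t-test (72% by normal approximation), whatever ρ is.
- Holm: power per score = P(Z1 > c_B) + P(c < Z1 ≤ c_B and Z2 > c_B). This is about 78% at ρ = 0, 77% at 0.5, 76% at 0.8 to 0.9, and 75% at 0.95.
- The chance of at least one significant score is the same under both rules: about 92% at ρ = 0, 86% at 0.5, 78% at 0.9 and 76% at 0.95.

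**The case against.** **The text does not prescribe two tests.** A reader might infer that the plan orders two uncorrected primary tests. The wording does not go that far. The outcome is a pain score in the singular, the analysis section speaks of scores but of one ANOVA, and the sample size uses one difference and one SD. A single summary score is a possible reading. This stands, and it limits the finding to a primary variable that is not uniquely defined and does not match its sample size. It does not rescue the plan, because no summary score is defined anywhere.

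**The rule may be elsewhere.** This is a condensed article, the analysis plan is not shown, and the article promises that all analyses are specified before data collection, with a blinded analyst. So the documents do not support saying that a split result will be settled after the data are seen. The absence of an analysis plan is not the complaint. The outcome definition and the sample-size basis are both set in this article, and they do not agree. A later rule would have to choose between the two named scores, define a combination, or change the alpha or power that applies.

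**The scores may be highly correlated.** Two ratings by one patient on one day may well be. High correlation shrinks the problem, but at 0.95 type I error is still 6.5% under the one rule and power is 77% under the other.

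**Conclusion.** The point holds as a mismatch between a two-score primary outcome and a one-score sample size. If both scores are tested at 0.05, the stated pair of 5% alpha and 80% power is not achieved. Type I error is about 9.8% to 6.5% if either score suffices, or power is about 65% to 77% if both are required. These ranges rest on a difference of 1 and SD 2 on each score and on correlations from 0 to 0.95. The direction does not depend on the correlation within that range.

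Two stronger readings are not supported. First, one might conclude that alpha and power both fail. No single rule breaks both: the either-score rule inflates alpha and leaves power above 80%, while the both-required rule keeps alpha and loses power. Second, one might conclude that 136 is miscalculated. It is exact for one score.

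The matter still deserves correction, because it governs the trial's main conclusion.

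**What to change.** Name one score as the single primary outcome in the objective, outcome, sample-size and analysis sections. Which score is the sponsor's choice; nothing in the article ranks one above the other. Test the other day-30 score next, at 0.05, only if the first is significant. N = 136 and 80% power then apply to the named score. A combined score defined in advance would also serve, provided that its SD is justified, since the calculation depends on SD 2.

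If both scores stay primary, state the decision rule and restate the power for N = 136:

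- both required: about 65% to 77%;
- Bonferroni at 0.025: about 71% per score;
- Holm: about 75% to 78% per score, with a chance of at least one significant score of about 76% to 92%.

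The correlation assumed should be stated with the figure.

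The cost is wording; no extra patients or data are needed. The downside is that under the fixed sequence the second score can be claimed only if the first is significant, and that keeping both means publishing a less favourable power figure.
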